## Abstract

**Introduction:** High levels of physical, cognitive, and psychosocial impairments are anticipated for those recovering from the COVID-19. In the UK, ~50% of survivors will require additional rehabilitation. Despite this, there is currently no evidence-based guideline available in England and Wales that addresses the identification, timing and nature of effective interventions to manage the morbidity associated following COVID-19. It is now timely to accelerate the development and evaluation of a rehabilitation service to support patients and healthcare services. Nuffield Health have responded by configuring a scalable rehabilitation pathway addressing the immediate requirements for those recovering from COVID-19 in the community.

**Methods and Analysis:** This long-term evaluation will examine the effectiveness of a 12-week community rehabilitation programme for COVID-19 patients who have been discharged following in-patient treatment. Consisting of two distinct 6-week phases; Phase 1 is an entirely remote service, delivered via digital applications. Phase 2 sees the same patients transition into a gym-based setting for supervised group-based rehabilitation. Trained rehabilitation specialists will coach patients across areas such as goal setting, exercise prescription, symptom management and emotional well-being. Outcomes will be collected at 0, 6, and 12 weeks and at 6- and 12-months. Primary outcome measures will assess changes in health-related quality of life (HR-QOL) and COVID-19 symptoms using EuroQol Five Dimension Five Level Version (EQ-5D-5L) and Dyspnea-12, respectively. Secondary outcome measures of the Duke Activity Status Questionnaire (DASI), 30 s sit to stand test, General Anxiety Disorder-7 (GAD-7), Patient Health Questionnaire-9 (PHQ-9), Patient Experience Questionnaire (PEQ) and Quality Adjusted Life Years (QALY) will allow for the evaluation of outcomes, mediators and moderators of outcome, and cost-effectiveness of treatment.

**Discussion:** This evaluation will investigate the immediate and long-term impact, as well as the cost effectiveness of a blended rehabilitation programme for COVID-19 survivors. This evaluation will provide a founding contribution to the literature, evaluating one of the first programmes of this type in the UK. The evaluation has international relevance, with the potential to show how a new model of service provision can support health services in the wake of COVID-19.

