18 years of age and over	Have a formal diagnosis of post-traumatic stress syndrome, clinically significant anxiety or depression where low intensity mental health intervention will not assist
Access to transport for phase 2 attendance	Have been diagnosed with Chronic Fatigue Syndrome

Once referred, the patient will complete an online pre-assessment health questionnaire. Once completed the questionnaire is made available digitally to a specialist trained physiotherapist who will contact the patient to conduct a telephone triage assessment. Following successful triage, the patient is handed on to a rehabilitation specialist who then takes up responsibility of the patients care. All patients will receive the identical 12-week programme structure consisting of two 6-week phases, depicted in Figure 1 and described in detail below.

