## Measures

Outcome data will be collected at 0, 6, and 12 weeks and again at 6- and 12-months post-intervention. Self-report data will be collected via digital application (MyWellbeing, Nuffield Health, London, UK). The patient will be emailed and provided a push-notification prompting them to complete the aforementioned questionnaires. Whilst this evaluation will not utilise any formal comparison group, it is intended that collaboration with trusts will support the analysis of anonymised “usual care” outcome data. This is likely to come from community physiotherapy and/or modified pulmonary rehabilitation.

All data will be securely stored on a dedicated Nuffield Health server and will be retained in line with the organisations publicly available data retention schedule. Modifications to data written to the database will be documented through via an internal inquiry system. Data entered into the database will be retrievable for viewing throughout by those granted secure access privileges associated with an identification code and password. Any data errors will be summarised along with detailed descriptions for each specific problem in a data query reports, which will be sent to the study Outcomes Analyst. The Outcomes Analyst will check any inconsistency, checking other sources to determine required corrections. Any coding changes required within the digital data capture system will then be implemented within 24 h.

Complete back up of the primary database will be performed twice a month. Incremental data back-ups will be performed on a daily basis. In addition to system back-ups, additional measures will be taken to back-up and export the database on a regular basis at site level. The outcomes analyst will send weekly email reports with information on missing data, missing forms, and missing visits to site level co-ordinators who will then rectify immediately as and when required. Data security audits will be completed by the Nuffield Health Information Security group on a quarterly basis. Full details of group membership and details of audit processes can be provided upon request.

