### Primary Outcome Measures

#### EuroQoL Five Dimension Five Level Version (EQ-5D-5 L)

This measure is used to assess a person's perception of their general health state and obtain a measure of quality adjusted life years (QALYs). Outcomes can be benchmarked against UK population norms. It covers five dimensions: mobility, self-care, usual activity, pain/discomfort and anxiety/depression, which are rated by the person on five levels of severity: no problems, slight problems, moderate problems, severe problems and extreme problems/unable to function within that domain (27).

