### Engagement and Usage Measures

The digital systems will collect anonymized descriptive data relating to engagement and usage of the service users with the platforms. Data collected will include the number of sessions attended, time spent in the platform, number of activities completed, number of minutes per log-in, number of resources accessed. A session is defined as an instance where a user logs on to the system. Session time will be always an imperfect calculation, as users may take breaks within a session, without formally log out of the system. To prevent this overestimation, periods of more than 30 min without interaction will be taken as 1 min and periods of inactivity longer than 3 h will start the count on a new session. Use of different program components will be measured.

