Examining potential mediators and moderators of change will contribute to our understanding of key processes in achieving improvement in services using blended models of rehabilitation. Whilst mediators and moderators of rehabilitation outcomes have been explored, this will be the first exploration of a combined digital/physical intervention. This will inform the tailoring of interventions to best address the needs of the targeted population, ultimately leading to the development of more effective interventions.

An area requiring on-going review and indeed development relates to the provision and impact of rehabilitation across sociodemographic groups. Black, low-income, and immigrant communities are particularly vulnerable and disproportionately impacted by COVID-19 (36, 37). Furthermore, data exists indicating that secondary care-based clinics may be underused by older populations and those in poorer socioeconomic circumstances (37). The proposed evaluation will ensure that sociodemographic variation is considered within analysis and that a representative sample from those that are disproportionately affected are consulted post-programme to understand barriers and facilitators. It is critical that learnings are continuous and that they are built into future re-iterations of the rehabilitation programme.

The proposed economic analysis will add to the current literature in regard to evidence of the cost-effectiveness of home or web-based rehabilitation programmes and will be an innovative analysis of a clinical rehabilitation programme ran independently of allied health professionals within a non-NHS community environment. In a context of health care provision where resources are now especially stretched, cost-effective interventions can only support the delivery of effective health services.

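### With one programme structure and no formal comparison group, the planned mediator and moderator work can show only predictors and correlates of change, so the tailoring claim goes too far

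*Protocol article*

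**What the plan says.** The Abstract lists the secondary measures and says that they "will allow for the evaluation of outcomes, mediators and moderators of outcome, and cost-effectiveness of treatment". The Discussion returns to this: "Examining potential mediators and moderators of change will contribute to our understanding of key processes in achieving improvement". It then draws the practical consequence: "This will inform the tailoring of interventions to best address the needs of the targeted population".

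The design is described under Trial Design: "All patients will receive the identical 12-week programme structure consisting of two 6-week phases". The Measures section opens its remark on comparators with: "Whilst this evaluation will not utilise any formal comparison group". It goes on to say that an analysis of anonymised usual-care outcome data is intended, in collaboration with the trusts.

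Of EQ-5D-5L, one of the two primary outcomes, the protocol says: "It covers five dimensions: mobility, self-care, usual activity, pain/discomfort and anxiety/depression". On process data, the section on engagement and usage says: "The digital systems will collect anonymized descriptive data relating to engagement and usage".

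**The concern.** A moderator changes the size of a treatment's effect, and a mediator carries part of that effect. To estimate either, one needs an estimate of the effect itself, and so a contrast between treated and untreated (or differently treated) patients that is not driven by the patients' own course. This cohort has no such contrast. What it can observe is who changes more and which measures change together.

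Patients discharged after COVID-19 can be expected to recover to some degree whatever is offered, and those who start worse have more room to move. Both processes would produce patterns that look like moderation and mediation in the absence of any programme effect. The Discussion says that learnings will feed into later versions of the programme, and Trial Design describes an intended expansion to all 112 centres. A tailoring rule built on such patterns could therefore reach a wide service, and it could be wrong even if the programme helps on average.

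**Working it through.** The protocol gives no effect size, power or error rate for this work, so there is no stated figure to reproduce. Three checks follow.

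**1. Regression to the mean.** Inputs (assumptions; none is in the protocol): no programme effect, baseline B and follow-up F each with SD 1, and correlation r between them of 0.5 to 0.8. Higher means worse, and scores are centred.

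- Expected follow-up given baseline: E[F | B] = rB.
- Expected improvement relative to the average patient: B − rB = (1 − r)B.
- Cov(B, F − B) = r − 1 and Var(F − B) = 2(1 − r), so corr(B, F − B) = −(1 − r)/√(2(1 − r)) = −√((1 − r)/2).

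| r | correlation of baseline with change | extra improvement if 1 SD worse at baseline |
|---|---|---|
| 0.5 | −√0.25 = −0.50 | 0.5 SD |
| 0.7 | −√0.15 = −0.39 | 0.3 SD |
| 0.8 | −√0.10 = −0.32 | 0.2 SD |

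This concerns baseline severity of the outcome set against raw change. It does not describe other candidate factors such as age or comorbidity; for those the difficulty is natural recovery, taken next.

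**2. Natural recovery without a comparator.** Simulation of 2000 cohorts of 160, the cap given under Trial Design. Everything else is assumed. The programme effect is zero. Natural recovery is R = 0.5 + 0.5X + standard normal noise, where X is a binary baseline factor that is purely prognostic. Change in the mediator and change in the outcome are each √s·R + √(1 − s)·independent noise, with s the approximate share of change due to recovery.

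- 'Mediation' is counted when the mediator improves and its change predicts outcome change, each at the 5% level.
- 'Moderation' is counted when X predicts outcome change at the 5% level.

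| s | 'mediation' found | median 'proportion mediated' | 'moderation' found |
|---|---|---|---|
| 0.3 | 98% | 0.31 | 39% |
| 0.5 | 100% | 0.51 | 61% |
| 0.7 | 100% | 0.71 | 75% |

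Hand check of one cell, s = 0.5: the difference in change by X is 0.5 × √0.5 = 0.354, its standard error is √(4/160) = 0.158, and the ratio is 2.24. The chance of exceeding 1.96 is about 61%, as simulated.

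The same data with a concurrent comparator (80 v 80, s = 0.5) gave moderation in 4.6% of runs and mediation in 5.0%, close to the nominal 5%. The excess comes from the missing contrast.

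**3. Content of the measures.** As the protocol describes them:

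| EQ-5D-5L dimension | counterpart among the secondary measures |
|---|---|
| mobility | DASI (ambulation) |
| self-care | DASI (personal care) |
| usual activity | DASI (household tasks) |
| anxiety/depression | GAD-7 and PHQ-9 |
| pain/discomfort | none |

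Four of the five dimensions have a counterpart. If change in DASI, GAD-7 or PHQ-9 were used to explain change in EQ-5D-5L, part of the association would be the same content measured twice. This does not apply to the 30 s sit to stand test, and it is not shown for Dyspnea-12, the other primary outcome.

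**The case against.** The strongest reply is that the text is hedged and peripheral. The Discussion speaks of potential factors and of an exploration. Mediators and moderators appear in neither the research questions and hypotheses (Aims) nor the Statistical Analysis section, and no primary conclusion depends on them. Exploratory predictors, together with the planned focus groups and the consultation on barriers and facilitators, can properly generate ideas for tailoring. All of this stands, and it keeps the point small. It does not cover the sentence saying that the work will inform tailoring, and no model in an unseen analysis plan could supply a contrast that the design lacks.

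The illustrations rest on assumed values, and the protocol plans mixed models rather than a regression of raw change on baseline. That is fair: they show the mechanism and a plausible size, not a forecast.

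A reader might also infer four stronger things that the protocol does not support:

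- *That treatment does not vary at all.* It is the structure that is common to all. Entry intensity is recommended for each patient (Rehabilitation Programme), one weekly session is chosen by the patient, and phase 1 may be repeated (Phase 1). Dose and duration do vary. But repetition follows insufficient progress, and session choice and intensity follow the patient's condition, so this variation is confounded with the outcome's own course.
- *That DASI, GAD-7 and PHQ-9 are the declared mediators of EQ-5D-5L.* No mediator or moderator is named. The overlap is therefore conditional, and it weakens a mediation reading without excluding one. Five time points would also allow lagged analyses.
- *That engagement is the only process measure free of overlap.* The sit to stand test is another.
- *That usage data cannot be linked to outcomes.* The Rehabilitation Programme section describes all research use of patient data as anonymous, yet mixed models need each patient's visits joined. The word may mean coded. Linkage is unclear, not ruled out.

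The intended usual-care data might in time offer a contrast, but they are only an intention.

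**Conclusion.** The concern holds in a limited form. With a common programme structure and no formal comparison group, the evaluation can identify baseline predictors of change and changes that are associated. It cannot establish moderators or mediators of the programme's effect, because neither pattern can be separated from natural recovery or regression to the mean. The statement that the work will inform tailoring therefore goes beyond the design.

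The size is illustrative. Regression to the mean alone gives 0.5 to 0.2 SD of extra improvement per 1 SD worse baseline, for an assumed r of 0.5 to 0.8 with equal variances. Under the assumed recovery model, apparent mediation is almost certain with no programme effect. Shared content would inflate the association further, but only if DASI, GAD-7 or PHQ-9 change is used to explain EQ-5D-5L change.

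Severity is minor: the aim is exploratory and outside the research questions and the stated analysis. That a mediation or moderation model is not set out is not held against the article.

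**What to change.** - In the Abstract and the Discussion, replace 'mediators and moderators' with 'exploratory baseline predictors and correlates of change'.
- Limit the tailoring statement in the Discussion to generating hypotheses for later comparative work. It need not be deleted.
- Analyse predictors on the follow-up score adjusted for its own baseline, not on raw change. This deals with the coupling in check 1. It does not remove natural recovery, so the results remain predictive only.
- Do not interpret change in DASI, GAD-7 or PHQ-9 as mediating change in EQ-5D-5L.
- Under Engagement and Usage Measures, clarify that usage data are held under a study ID so that they can be linked to outcomes.

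The cost is rewording in two places, one clarifying sentence and minor analysis work. If usage logs do not yet carry a study ID, one has to be added with matching data-protection wording. No further patients or outcome measures are needed. The downside is a more modest claim.

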## Summary

### Strengths and Limitations of This Study

Evaluates a critical and novel patient cohort.This evaluation will review the impact of digital and physical approaches to rehabilitation.Evaluates a new model of care delivery and the training of non-clinical staff.Demonstrates strong example of NHS/independent sector collaboration.A significant proportion of data will be self-reported due to COVID-19 restrictions.

## Ethics Statement

Manchester Metropolitan University Ethics Committee approved this study on 29/09/2020 (Ref: 25307). Informed consent will be gained from all participants prior to referral onto the rehabilitation programme. Consent will be captured digitally as part of the online referral programme. In review Participants will be contacted weekly to ensure that any clinical concerns are addressed and escalated where relevant. Processes are in place to inform the referring clinician and the participants general practitioner should medical intervention be required.

## Abbreviations

ARDS: Acute respiratory distress syndrome
AUC: Area under the curve
CIMSPA: The Chartered Institute for the Management of Sport and Physical Activity
CK: Creatine kinase
COVID-19: Corona virus disease
CPD: Continued professional development
EQ-5D-5L: EuroQoL Five Dimension Five Level Version
GAD-7: General anxiety disorder assessment-7
H7N9: Avian influenza
HR-QoL: Health Related Quality of Life
ICU: Intensive care unit
IL-6: Interleukin-6
MERS: Middle East respiratory syndrome
NHS: National Health Service
PEQ: Patient experience questionnaire
PHQ-9: Patient health questionnaire-9
PTSD: Post-traumatic stress syndrome
QALY: Quality adjusted life years
SARS: Severe acute respiratory syndrome.
